### Participants

Recruitment of community-dwelling older adult participants will occur through written English and Spanish language materials (flyers, posters, e-mail, and newspaper advertisement) and in-person group information sessions. Recruitment will occur in several places in the greater metropolitan area of Springfield, MA in an effort to have a diverse population of older adults in terms of sex, race, ethnicity, socioeconomic background, and education level. These places will include a local assisted living facility, several local senior centers, and healthcare facilities affiliated with Baystate Medical Center, Springfield, MA. Recruitment will be ongoing until the specified sample size is met (n = 90).

Before conducting any research activities, participants will be informed of the details of the study, permitted to ask questions, and sign an informed consent document. Participation in the study is expected to last for 12 months from the time of baseline measures.

Inclusion criteria are:

Adults aged ≥65 years who can ambulate household distances (16 m) with or without an assistive device

Have fall risk based on either:a. a “yes” to any of the Three Key Questions (Burns et al., 2022) [1) Do you feel unsteady when standing or walking? 2) Do you worry about falling? 3) Have you fallen in the past year?] orb. Have fall risk based on a Timed Up and Go score ≥12 s (CDC, 2023).

Participants will be excluded from participation if they have any of the following:• Poor foot sensation based on Semmes-Weinstein monofilament testing (Singh et al., 2005) (at least 5 of 9 sites on plantar foot have intact light touch sensation with 5.07/10 g filament).• Lower extremity amputations.• Lumbar spine or lower extremity injury or surgery in the past 6 months.• Impaired cognitive ability to follow verbal or written instructions based on the Mini Mental State Exam (score <24) (Tombaugh and McIntyre, 1992).• Vestibular disorders based on self-report or the Vestibular Screening Tool (score ≥4) (Stewart et al., 2015).• Participation in a fall prevention program in the previous 6 months.

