In addition to the above interventions, all participants will be given a pedometer (3D Fit Bud, 3D Active, United Kingdom) and asked to record daily step count in a paper journal. This will allow for comparisons of general physical activity level of each group. Also in the paper journal, participants will be asked to record any falls and the details of the circumstances should a fall occur. To promote intervention adherence and to capture details of falls while fairly recent, participants will be contacted every 2 weeks by researchers from 4 weeks post-intervention instruction to the end of the 12-month participation period. Participants may choose their communication preference for these contacts (email, phone call, or text message). With each contact, five standardized questions will be asked, and a reminder given to not participate in other fall prevention programs while enrolled in the current study:1. Have you experienced any falls (if yes, how many and can you provide details?)2. Are you performing the study activities and do you have any questions or issues?3. Are you using your journal?4. Are you using the pedometer and recording daily step count?5. Have you had any changes in health status?

All participants will be instructed in their intervention activities, pedometer use, and journal use by six trained Doctor of Physical Therapy (DPT) students. Two students will specialize in each group’s activities. Training for each group’s activities will include individual instruction and practice with the primary investigator, who is a physical therapist with 17 years of clinical experience. After instruction, practice, and individual feedback from the primary investigator, each DPT student will individually instruct a physical therapy faculty member unaffiliated with the study, and receive feedback. Written training materials for the DPT students are the same as the instructions that will be given to research participants and can be found in Supplementary Material.

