Hallux valgus angle is a simple clinical measure performed with a handheld goniometer with the participant seated with the hip, knee, and ankle joints at 90° and the foot resting on the floor. Hallux valgus is defined as ≥15° of abduction of the hallux from the first metatarsal, and has been further classified into stages of severity (mild 15°–25°, moderate 25°–35°, severe >35°) (Hagedorn et al., 2013). Greater hallux valgus angle has been linked to fall risk by several authors (Menz et al., 2006; Mickle et al., 2009; Koski et al., 1996). Measurement of hallux valgus is typically included in a comprehensive foot exam and was found to have good inter examiner reliability in a population of older adults (kappa values > 0.85, p < 0.01). (Hagedorn et al., 2013). When compared to the gold standard of radiographic measures of hallux valgus, clinical goniometry performed by an experienced clinician was within one°–5.5° (Janssen et al., 2014). Tang et al. conducted a 3 month intervention to reduce hallux valgus angle and found a reduction of 6.5° ± 3.8 resulted in significantly reduced pain and improved walking ability (Tang et al., 2002). Based on Tang et al.‘s work, we will consider a change of ≥7° to be a meaningful improvement. Although IFM function contributes to foot and toe alignment, we have included hallux valgus as an exploratory measure and do not anticipate it will significantly change in an older adult population. This can be likened to the malalignment of an osteoarthritic knee that does not change with exercise intervention alone (Raghava et al., 2001).

A physical therapist researcher with 17 years of clinical experience will perform all foot measures.

Fall Rate will be determined by the number of falls per person in the 12-month study period. Falls will be recorded based on journal entries and will be cross-referenced with subjective reports at 2-week contacts. Researchers and participants will use the operational definition of a fall as an unexpected event in which a person comes to rest on the ground or lower level (Laurence, 2021; Guirguis-Blake et al., 2018).

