#### Statistical analysis

Fall risk (MiniBESTest scores), muscle CSA of five IFM, Lower Extremity Position Test scores, navicular drop, and hallux valgus angle data will be compared using a *three-group x four-time points* repeated measures analysis of covariance (ANCOVA).

Fall rate will be measured using the number of falls per person in a 12-month period, beginning with the date of the baseline measure. A Cox proportional hazards model will be used to compare falls across groups.

Demographic and potential confounding variables will be collected and included in analyses (e.g., age, sex, height, weight, race, ethnicity, education, pre-trial physical activity (quantified based on the Physical Activity Guidelines for Americans, older adults) (Piercy et al., 2018), pre-trial falls history, comorbidities, medications, self-reported visual impairment, and grip strength).

Implementation variables will be analyzed quantitatively via adherence records and Likert scales, as well as qualitatively via semi-structured interviews.

Our primary analytic approach is an intention to treat analysis. We also will conduct a per protocol analysis for participants who do not complete all study activities (missing data). This may include analysis for mechanisms of missingness: missing completely at random (MCAR), missing at random (MAR) or missing not at random (MNAR). Based on the mechanism of missingness, we may perform a listwise or case deletion or last observation carried forward if appropriate. (Kang, 2013).

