### Potential limitations and solutions

We acknowledge a few limitations of this study, with possible solutions or mitigations.

Falls are multifactorial and caused by internal and external factors. The specific inclusion and exclusion criteria of this study attempts to minimize many internal confounding factors including poor foot sensation, vestibular disorders, cognitive impairments, amputations, and recent injury or surgery.

The participants will be asked to self-report falls, details of falls, intervention adherence, and step count in a paper journal. We recognize that self-reported data can be inaccurate or unreliable; however, we have mitigated this with a plan to contact participants every 2 weeks as a reminder and a supplemental way to collect this same data.

Our decision to collect foot measures using only the right foot is one based on time and resources for both researchers and participants. We recognize people can have asymmetry in the feet in terms of foot dominance, structure or pathology. Having only right foot measures limits the generalizability of our results.

The study will be conducted in an area of the United States with extremely cold winter weather. This may limit some participants’ ability to engage in the prescribed walking/wearing schedule of the minimal footwear. We will recommend people walk in minimal footwear in safe indoor spaces such as grocery stores or shopping malls, but accessibility to those spaces may be limited based on socioeconomic status. In addition, it is possible that participants wearing minimal footwear will be more unstable initially compared to their customary footwear. The walking/wearing schedule takes this into account with a very conservative increase in wear time to allow for the musculoskeletal and neuromuscular systems to gradually adapt to the footwear’s wider, thinner design.

This study addresses the very substantial clinical and community health issue of falls in older adults. The overall design and attention to detail will produce high quality research that may provide researchers, clinicians, policymakers, and older adults themselves with simple solutions to this highly relevant problem.

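### The fall outcome is defined as a 12-month rate per person, but the named Cox model, as ordinarily applied, estimates a first-fall hazard ratio and leaves repeat falls out

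*Protocol article*

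**What the plan says.** The outcome is defined twice, both times as a count per person. Under Outcomes: "Fall Rate will be determined by the number of falls per person in the 12-month study period". Under Statistical analysis: "Fall rate will be measured using the number of falls per person in a 12-month period, beginning with the date of the baseline measure". The next sentence of Statistical analysis gives the model: "A Cox proportional hazards model will be used to compare falls across groups". It does not say whether the event is the first fall or every fall, and it names no recurrent-event extension.

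Repeat falls are collected. Participants record falls in a journal, and the first scripted question at each two-weekly contact is "Have you experienced any falls (if yes, how many and can you provide details". Repeat falls are also to be expected, because one of the questions that qualifies a person for entry is "Have you fallen in the past year".

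On how the effect may change with time, Potential limitations and solutions says that "it is possible that participants wearing minimal footwear will be more unstable initially compared to their customary footwear" and describes a gradual wearing schedule in response. The Introduction puts growth of large muscle groups at 6 to 9 weeks of training at the earliest. The Intervention section lowers the prescribed frequency from 5 days a week to at least 2 after week 16.

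**The concern.** A rate of falls per person and a hazard of falling are different quantities. A standard Cox model follows each person to one event, so someone who falls once and someone who falls five times contribute the same single event. Its hazard ratio cannot be read as the ratio of fall rates that the outcome definition calls for. In a trial with 30 people per arm, setting aside every fall after the first also gives up information that is already being collected.

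A second, weaker worry is that one hazard ratio for the whole year assumes a constant effect. Possible early unsteadiness in new footwear, a delay before muscles respond and a lower frequency after week 16 all make that assumption uncertain.

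Third, the fall clock starts at the baseline measure. Allocation uses the baseline Mini-BESTest score (Randomization), and follow-up measurements are timed from intervention instruction (Outcomes). The clock can therefore start before a participant has an arm or an intervention.

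**Working it through.** **The plan's own figures.** There is no fall rate, hazard ratio, event count or sample size for falls. The only sample size, 22 per group for the Mini-BESTest, can be reproduced: a three-group analysis of variance with effect size f = 0.40, alpha 0.05 and power 0.80 needs 21.1, so 22. It says nothing about falls, and no stated number is overturned here.

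**Share of falls that are not first falls.** Assume that counts follow a gamma-Poisson (negative binomial) distribution with mean m per year and dispersion k, with full 12-month follow-up.

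- Probability of no fall: p0 = (1 + k·m)^(−1/k).
- Expected first falls per person: 1 − p0. Expected falls per person: m.
- Share unused by a first-fall model: 1 − (1 − p0)/m.
- Example, m = 1 and k = 1: p0 = 1/2, so the share is 1 − 0.5/1 = 0.50.

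| Falls per person-year (assumed) | k = 0.5 | k = 1 | k = 2 |
|---|---|---|---|
| 0.6 | 0.32 | 0.38 | 0.46 |
| 1.0 | 0.44 | 0.50 | 0.58 |
| 1.5 | 0.55 | 0.60 | 0.67 |
| 2.0 | 0.62 | 0.67 | 0.72 |

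With early leavers and a halved rate in the active arm, the share is lower. At a control rate of 1 per year and 30% leaving early, a simulation gave 38.6 falls and 22.4 first falls on average: (38.6 − 22.4)/38.6 = 42%.

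**Power and effect measure.** Simulation of 30 against 30, full follow-up, constant true rate ratio 0.5, 600 runs, first-fall Cox against negative binomial. The gap is taken from unrounded values.

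| Control rate, k | Cox power | Neg. binomial power | Gap (points) | Median hazard ratio | Median rate ratio |
|---|---|---|---|---|---|
| 1.0, 0.5 | 33.8% | 51.0% | 17.2 | 0.56 | 0.49 |
| 1.0, 1 | 24.2% | 41.8% | 17.7 | 0.58 | 0.50 |
| 1.5, 0.5 | 39.5% | 57.2% | 17.7 | 0.54 | 0.50 |
| 1.5, 1 | 26.8% | 49.8% | 23.0 | 0.60 | 0.50 |

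With 30% leaving early and k = 1, power was 25% against 38% at 1 fall per year (13 points), and 27% against 47% at 1.5 (20 points). Across both settings the gap is about 13 to 23 points. With 600 runs, the Monte Carlo standard error of each power figure is at most √(0.5 × 0.5/600) = 2 points. Wald tests from small negative binomial fits can be slightly anti-conservative, so the gap is approximate.

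Even with a constant rate ratio of 0.5, the first-fall hazard ratio lies at 0.54 to 0.60, because people differ in their tendency to fall. The two measures are not interchangeable.

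**An effect that changes with time.** Assume a ratio of 1.3 for 16 weeks, then 0.5. The average over the year is 1.3 × 16/52 + 0.5 × 36/52 = 0.40 + 0.35 = 0.75. The simulated Cox hazard ratio was 0.84 to 0.92 and the negative binomial rate ratio 0.74 to 0.77, with power of 6 to 8% and 12 to 19%. Both summaries lie below 1, so neither shows the early excess.

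**The case against.** The strongest reply is that the article never says the event is the first fall. Recurrent-event Cox models with robust variance use every fall, and the form of the model could be set out in an analysis plan that is not shown. In a rerun with 30% leaving early and k = 1, such a model had 38% power at 1 fall per year and 44% at 1.5. Negative binomial had 38% and 45%, and first-fall Cox 25% at both rates. The power loss thus comes from the first-fall reading and not from Cox as such. This stands. It does not remove the mismatch, because the article fixes both a rate as endpoint and a model whose usual form does not estimate one.

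A reader might infer more than the document supports:

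- *That the plan's own text contradicts proportional hazards.* It says only that early instability is possible, for one of three arms and relative to participants' own usual shoes. It adds a mitigation, a "very conservative increase in wear time to allow for the musculoskeletal and neuromuscular systems to gradually adapt". The hypotheses under Anticipated results do not mention fall counts or their timing. Doubtful is fair; contradicted is not.
- *That early leavers are mishandled.* Cox censors them. Only the raw count in the definition lacks a person-time denominator.
- *That the early weeks go unobserved.* The scripted contacts do start late: "participants will be contacted every 2 weeks by researchers from 4 weeks post-intervention instruction to the end of the 12-month participation period". But the journal is the main fall record, its use is taught at intervention instruction, and there are reviews at 1 and 4 weeks.
- *That a count model would expose early harm.* It would average over it too, as the last calculation shows.

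The Mini-BESTest is the primary measure, and the trial is not powered on falls under any model.

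**Conclusion.** The mismatch between endpoint and model is real and stated in the text: a rate per person is defined, and a Cox model with no recurrent-event form is named. Under the usual first-fall reading, about one third to 70% of falls would go unused at 0.6 to 2.0 falls per person-year and dispersion 0.5 to 2. The cost would be about 13 to 23 points of power for a rate ratio of 0.5 with 30 per arm. These sizes rest wholly on assumed rates, dispersion and effect, and on that reading; a recurrent-event Cox model would recover nearly all of the loss. A constant hazard ratio is doubtful but not contradicted. The baseline start of the clock is a smaller defect of unknown size, because the interval from baseline to instruction is not given. Severity is moderate, since falls are a non-primary outcome. Even the count model exceeded 50% power in only two of the four full-follow-up scenarios, so a null result on falls should not be read as no effect.

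**What to change.** - **Main analysis of falls.** Compare fall rates by negative binomial regression: total falls as outcome, log of observed person-time as offset, group as factor, and falls in the year before the trial and the randomisation strata (sex, age band, Mini-BESTest category) as covariates. Report a rate ratio with confidence interval for each active arm against control. A recurrent-event Cox model with robust variance is an acceptable alternative if it is named as such.
- **Secondary analysis.** Keep Cox for time to first fall, labelled so, with a check of proportional hazards.
- **Fall clock.** Start it at randomisation or intervention instruction, the same for all arms, and use that date for person-time.
- **Early falls.** Tabulate falls by arm for the first weeks separately, because one 12-month ratio of either kind averages over an early excess.

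The cost is a few sentences of analysis wording and one changed start date. Fall counts, prior-year falls and strata are already collected, so no extra participants, visits or measurements are needed. The change should be made before outcome data are examined by arm.

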**FIGURE 1 F1:**
[figure not shown]
Examples of intrinsic foot muscle (IFM) strengthening exercises: **(A)** foot at rest; **(B)** great toe lift; **(C)** small toes lift; **(D)** toe spread; **(E)** foot at rest; **(F)** short foot exercise or “doming” – note the skin folds as the muscles contract and creates greater arch height.

In two studies by Ridge et al. of young healthy adults, they found that minimal footwear use with daily activities increased IFM size and strength as much as IFM strengthening exercises (Ridge et al., 2018), and that progressive time spent walking in minimal footwear increased IFM size and strength (Ridge et al., 2019). While the effects in older adults are not yet known, a small study of 4 months of minimal footwear use in older adults showed improvements in lower extremity pain, foot sensation, and overall function (Franklin et al., 2017a; Trombini-Souza et al., 2015). Researchers speculated the minimal footwear may enhance neuromuscular stimulation or proprioception in the feet, leading to improvements in gait and balance—key protective factors for falls (Fraser and Hertel, 2019b; Arnold and Menz, 2023).

Limited research on IFM strengthening exercises for older adults is promising, demonstrating increased IFM strength with supervised training (Futre et al., 2022; Mickle et al., 2016b). Increased large muscle group cross-sectional area (an indication of hypertrophy and increased strength) occurred in as little as 6–9 weeks of strength training in older adults (Mayer et al., 2011). The same may be possible for the IFM in an older population, although it may take longer in deconditioned or frail individuals (Borst, 2004). It is unknown if IFM strength increases, with minimal footwear or specific exercises, result in reduction of falls, fall risk, or improved mobility.

The objective of this study is to assess the effects of two IFM strengthening interventions in older adults compared to a control intervention, focusing on the effects on IFM cross-sectional area (CSA), proprioception, foot structure, and fall risk. Results may inform fall prevention interventions for older adults. This study is registered at ClinicalTrials.gov (NCT05829369). The study received Institutional Review Board approval by the lead investigator’s institution (Springfield College, Springfield, MA), approval #1492223. The protocol for this project follows the Consolidated Standards of Report Trials (CONSORT) checklist.

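### Falls are defined as a rate per person, but the only model named is a Cox model with no recurrent-event form, which by default analyses time to first fall

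*Protocol article*

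**What the plan says.** The fall outcome is defined twice, each time as a count per person.

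- Outcomes, closing paragraph of the foot-structure subsection: "Fall Rate will be determined by the number of falls per person in the 12-month study period".
- Statistical analysis: "Fall rate will be measured using the number of falls per person in a 12-month period, beginning with the date of the baseline measure".

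The next sentence of Statistical analysis gives the comparison: "A Cox proportional hazards model will be used to compare falls across groups". The article names no count or rate model, no time-to-first-fall endpoint, no recurrent-event extension, and no robust variance or frailty term.

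Repeat falls are collected on purpose. The two-weekly contact described under Intervention asks "Have you experienced any falls (if yes, how many and can you provide details", and the outcome paragraph adds "Falls will be recorded based on journal entries and will be cross-referenced with subjective reports at 2-week contacts". They are also plausible in this population, because one of the screening questions that can qualify a participant is "Have you fallen in the past year".

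**The concern.** A count over a fixed period and a time-to-event model answer different questions. Unless it is extended to recurrent events, a Cox model uses each person's time to first fall and removes that person from the risk set afterwards. The result compares how soon people become fallers, whereas the stated outcome calls for a ratio of fall rates. Three things follow under that default reading:

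- Second and later falls, which the diaries and contacts are set up to capture, do not enter the comparison.
- If people differ in fall-proneness, the first-fall hazard ratio drifts toward 1 even when the rate ratio is constant, so the reported effect is smaller than the effect on the rate.
- Precision is lost on the only outcome that counts actual falls.

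Proportional hazards is also open to doubt if benefit builds up during training. The Introduction says of muscle growth "although it may take longer in deconditioned or frail individuals", and the limitations section describes "a very conservative increase in wear time" for the footwear. Left as it stands, the trial would either report something other than the rate it defines, or settle the handling of repeat falls after the data are in.

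**Working it through.** **Plan's own figure.** There is none to reproduce. The sample-size section powers the Mini-BESTest only; no fall rate, event count or power for falls is given.

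**Inputs.** From the article: 30 participants per group, alpha 0.05, 12 months of follow-up. Assumed, because the documents are silent: mean falls per person-year *m*, between-person dispersion *k* (the gamma variance θ), rate ratio RR, a two-sided test, full follow-up and no covariate adjustment.

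**Step 1: share of falls that a first-fall model uses.** Share = P(at least one fall) / *m*, with P(0) = exp(−*m*) if *k* = 0 and P(0) = (1 + *km*)^(−1/*k*) otherwise.

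| Mean falls per year | *k* = 0 | *k* = 1 | *k* = 2 |
|---|---|---|---|
| 0.5 | 79% | 67% | 59% |
| 1 | 63% | 50% | 42% |
| 2 | 43% | 33% | 28% |
| 3 | 32% | 25% | 21% |

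For two arms with means 1 and 0.5 and *k* = 1, the probabilities of at least one fall are 1 − 1/2 = 0.500 and 1 − 1/1.5 = 0.333. The share is (0.500 + 0.333) / 1.5 = 56%; simulation gave about 57%.

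**Step 2: what the hazard ratio estimates.** Under gamma heterogeneity with a constant rate ratio and control rate λ, the first-fall hazard ratio at time *t* is

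HR(*t*) = RR(1 + θλ*t*) / (1 + θ·RR·λ*t*).

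With λ = 1, θ = 1, RR = 0.5:

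- at *t* = 0 it is 0.50;
- at *t* = 1 year it is 0.5 × 2 / 1.5 = 0.67.

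The Cox estimate averages over this drift. In large simulated samples (20,000 per arm) with a true rate ratio of 0.6, the first-fall hazard ratio was about 0.60–0.61 with no heterogeneity, 0.70–0.71 at *k* = 1 and 0.69–0.76 at *k* = 2. It matches the rate ratio only when there is no heterogeneity.

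**Step 3: power for one comparison of 30 against 30.** With 1 fall per person-year, gamma variance 1 and RR = 0.5, separate simulations gave:

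- first-fall Cox: hazard ratio 0.57–0.58, power 22–28%;
- negative binomial on all falls: rate ratio 0.48–0.50, power 40–43%.

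At other assumed values with RR = 0.5, power was:

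| Mean falls per year | *k* | First-fall Cox | Negative binomial |
|---|---|---|---|
| 1 | 0.5 | 32% | 50% |
| 1 | 2 | 20% | 35% |
| 2 | 0.5 | 43% | 67% |
| 2 | 1 | 31% | 56% |
| 2 | 2 | 18% | 38% |

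**Step 4: test size and weaker effects.** Type I error was 4–6% for Cox and 5–8% for negative binomial, so part of the raw gap comes from a liberal test. After size adjustment at *m* = 1, *k* = 1, RR = 0.5, power was 39% (negative binomial) against 29% (Cox) with 30 per arm, and 28% against 22% with 22 per arm. At RR = 0.75 with 30 per arm it was about 13% against 9% unadjusted, and about 10% against 9% size-adjusted.

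**The case against.** **Falls are not primary.** The sample-size section names the Mini-BESTest as the primary measure, the objective speaks of fall risk rather than fall rate, and the anticipated results make no prediction about fall rate. This stands and limits the severity.

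**First-fall use is not stated.** The article never says that follow-up ends at the first fall, and event coding is a detail that an analysis plan could supply. A reader might infer that repeat falls will certainly be discarded; the text does not say so. First-fall use is the default reading of the model as named, and the loss is conditional on it. The mismatch remains, because the article itself fixes both a rate outcome and a model that does not, as named, estimate a rate.

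**Proportional hazards.** A reader might infer from the 16-week training and the gradual wear schedule that proportionality must fail. The documents do not show this. The remarks on slow change concern muscle size and shoe wear, no time course is given for falls, and the Introduction says it is unknown whether strength gains reduce falls at all. A gradual effect would also dilute the rate ratio: with a linear build-up over 16 weeks and the base inputs, the negative binomial estimate moved from 0.50 to 0.57 and the Cox estimate from 0.58 to 0.66.

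**Assumed inputs.** Rate, dispersion and effect are not in the documents, and the runs ignore both the 30% attrition planned for and the covariates listed. Adjusting for falls history and comorbidities would absorb some of the heterogeneity behind the drift. This stands: the direction is secure, the size is not.

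**Validity.** First-fall Cox held its type I error at 4–6%. The cost is a different estimand and lost efficiency, not a false-positive problem.

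**Conclusion.** The mismatch is in the text: a per-person fall rate, with every fall collected, is paired with a Cox model for which no recurrent-event form is named. On the default reading, the analysis omits repeat falls and estimates a hazard ratio for becoming a faller. That ratio lies closer to 1 than the rate ratio whenever people differ in fall-proneness. Under the illustrative inputs, a rate ratio of 0.5 appears as a hazard ratio of about 0.57, and power is 22–28% instead of 40–43%. These figures rest on an assumed rate, dispersion and effect, full follow-up and no adjustment. Even with no heterogeneity, when the two ratios agree, 37% of falls would go unused at a mean of one per year.

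It would be wrong to conclude that a count model rescues the falls comparison. At a rate ratio of 0.75 both models have power of about 13% or less, so neither is adequate. Proportional hazards is doubtful but not shown to fail. This should be fixed; it does not touch the primary measure or any power claim.

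**What to change.** In Statistical analysis, replace the Cox sentence with one of two choices:

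- negative binomial regression of each participant's fall count, with arm as a factor and log observed time as offset, reporting rate ratios with 95% confidence intervals; or
- a recurrent-event Cox model (Andersen-Gill) with robust standard errors.

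The first follows the stated outcome most directly, and the offset uses the partial follow-up of those who leave early. With about 30 per arm, a slightly liberal test should be acknowledged. Keep time to first fall by Cox regression as a supportive analysis, labelled as such.

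The cost is a sentence or two. The journals and two-weekly contacts already record every fall, so no new data are needed.
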